## Discussion

The proposed protocol provides a general overview of the research methodology of the study WE_SENSE_THE_NATURE. The purpose of this study is to increase the knowledge about the impact of the natural environment on well-being and health, providing more information to both health professionals and the public. We will conduct an experimental study including individuals with CAD attending cardiac rehabilitation. We hypothesize that psychophysiological reactions to stress in individuals with CAD will differ with respect to the walking environment (between OUT and IN group walking in nature vs. gym respectively) and weather sensitivity (between WS and non-WS individuals who experience a weather sensitivity or lack of weather sensitivity).

This randomized controlled trial will be the first to investigate the influence of walking in different environments on psychophysiological responses to stress of individuals with CAD during rehabilitation, and to evaluate the importance of the weather sensitivity profile. This research project might provide important insight on the importance of environmental exposure, as it is still an underappreciated risk factor contributing to the development and severity of heart disease.

Additionally, findings on personality traits and cognitive functions (especially cognitive flexibility) in relation to WS may reveal significant information which could help to even better stratify and individual treatment possibilities available for stress-vulnerable individuals with CAD. Weather sensitivity profiling in the context of personality type and individual’s cognitive flexibility might prove to be useful in adapting personalised regimen of physical activity in cardiac rehabilitation.

Understanding the nature of the environmental impact on the human body could aid in the preventive treatment of a broad spectrum of health disorders [20]. Despite significant advancements in prevention and control, CVDs continue to be a leading cause of health problems and deaths worldwide [21], including Lithuania [22]. CVD treatment requires a comprehensive approach owing to its significant effects on healthcare services. While traditional risk factors, such as smoking, alcohol use, hypertension, high cholesterol levels and obesity, are fundamental in explaining a substantial number of CVDs, numerous features of the environment have been discovered to have a significant impact on CVD risk, development, and course [18]. For instance, many studies have focused on the role of extreme temperatures in cardiovascular emergencies. Heat exposure has been linked to a higher risk of cardiovascular emergencies [46], although some authors have shown that this relationship is only present above a certain temperature threshold [47]. On the other hand, low temperatures have also been associated with higher CVD risk [48]. Other climatic factors may also influence cardiovascular health. Wind velocity, atmospheric pressure, and sunshine exposure have been linked to a higher incidence of myocardial infarction (MI) [49]. However, the exact role of many environmental variables in CVD remains unclear, with some studies showing contradictory results. Among these variables is precipitation, with some authors finding no consistent role of rain- or snowfall in the incidence of acute coronary syndromes [50], whereas others have demonstrated a relationship between snowfall and MI-related hospitalisation or death [51]. Such discrepancies could possibly result from varying weather conditions depending on the location of the study. Moreover, the snowfall-MI risk relationship has been shown to be stronger in men [50]. This highlights the necessity of considering both regional and individual variability when considering the role of weather in CVD. Therefore, assessment of the potential contribution of environmental factors to the course of CAD is important, as many such factors are modifiable either through individual behaviors or government regulation, and early intervention has the potential for significant public health benefits [48].

Rehabilitation is one of the main aspects included in CVD medical care. Cardiac rehabilitation programs aim to reduce the risk of another heart event, to monitor and control the current heart condition, and to improve the health and quality of life of patients with CVDs [7]. A cardiovascular rehabilitation program includes standard secondary CVD prevention according to current guidelines, including physical therapy with daily outdoor walks [7].

To date, there are no clear pathophysiological links between weather and cardiovascular diseases. Climatic stress may increase direct and indirect risks to human health via different, complex pathophysiological pathways and exogenous and endogenous mechanisms [52]. Heat may compromise the cardiovascular system by causing dehydration, vasodilation, changes in coagulation, and damage to the vascular endothelium, which may ultimately result in an autonomic imbalance and pose a risk of hemorrhage and thrombosis [46]. On the other hand, cold exposure can pose a risk to the cardiovascular system by causing a rise in myocardial oxygen demand, increasing cholesterol build-up in atherosclerotic plaques, and promoting hypercoagulability [48]. This duality may explain why many authors have reported a non-linear, often U-shaped, relationship between temperature and cardiovascular mortality [2]. Therefore, both extremely cold and extremely hot conditions can pose a threat to cardiovascular health. The unfolding of climate change comes with a bigger range of temperature oscillations and more extreme weather events and might therefore pose a tangible risk for CAD patients.

Awareness about the potential influence of weather sensitivity on the psychophysiological reactions to stress in patients with CAD is much needed as it may contribute to a timely planning and implementation of actions leading for improved medical care services and preventive measures, in the face of the expected climate change. This in turn, would help to avoid the worsening of health and well-being in the future. Protective measures should be directed towards susceptible groups rather than the entire population. The outcomes of this experiment may have direct contribution to three fields:

clinical practice - using different types of environments in cardiac rehabilitation. If the hypotheses are confirmed, for weather-sensitive patients with CAD, it might be better to engage in physical activity in an indoor environment than in an outdoor one;sciences and education. Whilst the study will be carried out in Lithuania, it is hoped that the methods used and the results obtained will contribute to a better understanding of the problem analyses and will be useful for future insights and research not only in Lithuania, but also on an international level. It might also provide a foundation for new research studies looking into and beyond traditional risk factors identifying high-risk subgroups of patients with CAD vulnerable to stress.health services’ management - to the government and policymakers in planning and implementing actions to improve medical care services in rehabilitation and post-rehabilitation settings.

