## Methods / design

### Aim

The aim of this study is to investigate how WS and walking in different environments affect psychophysiological responses to the stress of individuals with CAD during rehabilitation.

To achieve the main goal, we will aim to deliver a set of specific objectives:

Determining how walking outdoors (in a natural setting) affects the psychophysiological reactions to stress in individuals with CAD.Determining how walking indoors (in the gym) affects the psychophysiological reactions to stress in individuals with CAD.Investigating the associations between the psychophysiological reactions to stress of individuals with CAD and the walking environment, by accounting for their weather-sensitivity.Understanding the connections between mental flexibility and weather sensitivity in the context of personality characteristics and mental distress.

We hypothesize that: (1) the psychophysiological reactions to stress in people with CAD will differ between the experimental (walking outdoors) and the control group (walking indoors); (2) for the experimental group, we hypothesize that psychophysiological reactions to stress will differ between WS individuals and non-WS individuals, showing more favorable results in the latter subgroup (non-WS individuals); (3) for the control group, we hypothesize that psychophysiological reactions to stress will differ between WS individuals and non-WS individuals, showing more favorable results in the former subgroup (WS individuals). The fourth goal is exploratory and therefore has no hypothesis.

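### Confirming the three hypotheses would not show that weather-sensitive patients do better indoors; the indoor-outdoor contrast among those patients has to be stated

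*Protocol article*

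**What the plan says.** The Aim section gives three hypotheses.

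- **H1:** stress reactions "will differ between the experimental (walking outdoors) and the control group (walking indoors"). This covers all patients and names no direction.
- **H2:** "for the experimental group, we hypothesize that psychophysiological reactions to stress will differ between WS individuals and non-WS individuals". The predicted direction is added there as "showing more favorable results in the latter subgroup (non-WS individuals").
- **H3:** "for the control group, we hypothesize that psychophysiological reactions to stress will differ between WS individuals and non-WS individuals". Here the predicted direction is reversed: "showing more favorable results in the former subgroup (WS individuals").

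Objective 3 in the same section concerns the association between stress reactions "and the walking environment, by accounting for their weather-sensitivity". The opening of the Discussion restates the hypotheses as two factors: reactions "will differ with respect to the walking environment (between OUT and IN group walking in nature vs. gym respectively) and weather sensitivity".

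Later in the Discussion, under the contribution to clinical practice, the article says: "If the hypotheses are confirmed, for weather-sensitive patients with CAD, it might be better to engage in physical activity in an indoor environment", as against an outdoor one. No hypothesis compares indoor with outdoor walking among WS patients.

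**The concern.** The clinical sentence is about choosing an environment for a WS patient. The comparison that answers it is outdoor against indoor among WS patients. H2 and H3 run the other way: they hold the environment fixed and compare two kinds of patient. H1 compares the environments but mixes both kinds of patient and has no direction.

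The type of contrast matters too. Walking environment is what the trial allocates. Weather sensitivity is a characteristic that patients bring with them, so H2 and H3 are observational. The protocol itself studies personality, mental distress and cognition as correlates of WS, and Table 1 treats mental health status as a confounder. A WS versus non-WS difference within an arm may therefore reflect those correlates.

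At stake is a subgroup statement about cardiac patients that could be made with every hypothesis confirmed while the trial's own means for that subgroup point the other way.

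**Working it through.** **1. What H2 and H3 imply.** Write O and I for the outdoor and indoor means, with subscripts W (WS) and N (non-WS); higher is more favourable.

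- H2: O_N − O_W > 0
- H3: I_W − I_N > 0
- Sum: (I_W − O_W) − (I_N − O_N) > 0

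The indoor-minus-outdoor difference is thus more favourable in WS than in non-WS patients, which is an interaction. Adding a constant to both outdoor means leaves H2 and H3 untouched but shifts I_W − O_W by that constant, so its sign is free.

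**2. Counterexample (illustrative scale, half of each arm WS).**

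| | non-WS | WS | arm mean |
|---|---|---|---|
| Outdoor | 6 | 5 | 5.5 |
| Indoor | 3 | 4 | 3.5 |

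H1 holds (5.5 v 3.5), H2 holds (6 > 5) and H3 holds (4 > 3). Among WS patients, indoor minus outdoor is 4 − 5 = −1, so they do better outdoors. Now take 4 off both outdoor means (non-WS 2, WS 1, arm mean 1.5). All three hypotheses still hold, and the WS difference becomes 4 − 1 = +3. The same confirmed hypotheses fit both answers.

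**3. Significance of both within-arm tests.** With equal cells, two z values beyond 1.96 in the predicted opposite directions give an interaction z of at least (1.96 + 1.96)/√2 = 2.77. Joint confirmation therefore does establish interaction. What it does not give is the effect of environment within WS patients.

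**4. Power.** The protocol gives no power figure for any WS contrast, so there is none to reproduce. Inputs:

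- N = 164 and d = 0.5, from Sample size.
- About 50% WS, from the team's earlier study cited in Background; 40–60% is my assumed range.
- Alternating allocation, hence equal arms, from Randomisation.
- Alpha 0.05 is assumed, because neither alpha nor sidedness is given.

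Cell size at 50% WS: 164 × 0.5 / 2 = 41.

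| Test | Power |
|---|---|
| Outdoor v indoor within WS, d = 0.5, 41 v 41, two-sided | 0.61 |
| Same, one-sided | 0.73 |
| Same, two-sided, after 4% attrition (41 × 0.96 = 39.4 per arm) | 0.59 |
| Same, two-sided, 40% WS (about 33 per arm) | 0.52 |
| Same, two-sided, 60% WS (about 49 per arm) | 0.69 |
| Interaction of 1.0 SD, two-sided | 0.89 |
| Interaction of 0.5 SD, two-sided | 0.36 |

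The first five rows use the noncentral t distribution. The interaction rows use standard error √(4/41) = 0.312 SD and an F test on 160 degrees of freedom. An interaction of 1.0 SD corresponds to 0.5 SD in each direction under H2 and H3.

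The H2 and H3 tests also compare 41 with 41, so each has power 0.61 two-sided. Both succeed with probability 0.61² ≈ 0.37, or 0.73² ≈ 0.53 if run one-sided in their stated directions.

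**The case against.** **The sentence is hedged.** It says only that indoor activity might be better. The Limitation section calls the study a pilot and asks for replication before recommendations are made. A reader might infer that the trial would issue advice to WS patients on the strength of H2 and H3; the article does not say that. This lowers the severity. It does not repair the inference, because a hedge weakens a conclusion without supplying the comparison behind it.

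**H1 would be seen alongside.** In the counterexample H1 comes out in favour of outdoor walking, and a careful author would notice. Part of this stands. If H1 favoured indoor walking, and the WS share were equal in the two arms, the WS conclusion would follow: the overall difference is a weighted average of the two subgroup differences, and by H2 and H3 the WS one is the larger. But H1 is stated without direction, and the Background leans towards outdoor exercise. If H1 favours outdoors, the sign within WS stays open.

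**The analysis may already cover it.** Objective 3 and the general linear model under Statistical analysis could accommodate an arm-by-WS term. That is fair, and the absence of a named interaction term in a condensed article is not the point here. A reader might also infer that two within-arm results say nothing about whether the environment effect depends on WS. That is too strong: in opposite directions they do (step 3), though less efficiently than one interaction test.

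**The right contrast is no better powered.** Also true. At 0.61 it matches each within-arm test. That is a reason to report an interval; it does not justify substituting a different contrast.

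**Conclusion.** The point holds as a matter of logic and needs no power assumption: H1, H2 and H3 can all be confirmed while WS patients do better outdoors, so the clinical sentence in the Discussion does not follow from the Aim section. The fault lies in what the article itself states, since an analysis that implemented H2 and H3 faithfully would carry it forward.

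Its reach is limited. The overall outdoor versus indoor comparison is unaffected, and the documents do not support saying that the trial will recommend indoor exercise or that it cannot detect effect modification. Given the hedged wording and pilot status, it should be fixed before analysis but does not threaten the trial.

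The power figures rest on two-sided alpha 0.05, d = 0.5 and about half the patients being WS. Over 40–60% WS, the contrast within WS patients has power of about 0.52 to 0.69.

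**What to change.** 1. Fit one model for the outcome with arm, WS, arm × WS and the pre-walk baseline value. Report the interaction, and the outdoor-minus-indoor difference with its 95% CI separately in WS and non-WS patients.
2. Rest the clinical-practice sentence only on the difference within WS patients. Alternatively, limit the sentence to what H2 and H3 can show: that the indoor-outdoor difference varies with weather sensitivity.
3. Keep the within-arm WS versus non-WS differences as descriptive.
4. State in advance one definition of WS for this analysis. Table 1 lists both the 11-item diary and a single yes/no question.
5. State the power of the contrast within WS patients (about 0.61 at d = 0.5 under the assumptions above) and present the subgroup result as an estimate with its interval.

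The cost is wording in the protocol and analysis plan. Data, allocation and sample size do not change. The downsides are that H2 and H3 become descriptive and that the contrast replacing them is imprecise at this sample size.

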### Strengths of the study

This research offers a more integrative approach to understanding of the processes that contribute the psychophysiological stress response in CAD patients, by accounting for both the dispositional and the situational factors.The study could provide deeper insight the effects of walking in nature (vs. gym) on the psychophysiological stress response in individuals with CAD, by accounting for their sensitivity to weather (and profiling them accordingly), as well as a set of other parameters.

### Limitation

Participant recruitment from a single cardiac rehabilitation centre may have subject our results to selection bias. Additionally, it might lead to a prolonged recruitment procedure (lasting up to one year), in order to obtain optimal sample size.

We will measure cortisol levels during early recovery period which will preclude us from reporting the data on cortisol variability during late recovery periods (for example next day measures).

Finally, we consider this as a pilot study, thus similar replication studies are warranted for future research to guide the recommendation process.

## Data Availability

No datasets were generated or analysed during the current study.
